**Fig. 1 Fig1:**
[figure not shown]
Overview of the Amandla Mama Study Methodology

In Phase 1 the Amandla Mama videos will be iteratively developed through, (i) scripting, (ii) storyboard development, and (iii) refining the developed storyboards by incorporating formative qualitative feedback from expectant mothers, their partners, and health workers gathered through in-depth interviews.

During Phase 2 of the study, the Amandla Mama videos, developed in Phase 1, will be tested using a randomized control trial. Participants will be expectant mothers and their partners living in South Africa accessing routine perinatal healthcare services. The intervention group will watch the Amandla Mama Videos, and the control group will receive treatment as usual for antenatal care only. Treatment as usual antenatal care consists of standard maternity care, as outlined in the South African National Department of Health’s “*Guidelines for Maternity Care in South Africa*” [10]. Maternity care is offered free of charge in the South African public health sector and is integrated into primary healthcare [10]. A survey will be used to gauge whether the intervention results in knowledge change. The surveys, developed by the research team, have been designed to measure change in maternal knowledge, intended behavior, and, user satisfaction. These will be administered to patients 3 months after receiving the intervention. Surveys will also be conducted with partners of the recruited expectant mothers in the study, given the documented benefits to mothers having partners participate in accessing maternal health care services. The partner surveys will have the same content as those designed for the expectant mothers but will be adapted to be relevant to the partner. Knowledge will be the primary outcome and intended behavior change will be the secondary outcome of this randomized control trial.

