### Study population

The study population includes expectant mothers, 18 years or older attending antenatal care services, pregnant women’s partners, and health workers. Expectant mothers without partners will not be excluded from participating in our study.

The inclusion criteria for expectant mothers and their partners include:Expectant mothers and their partners must be 18 years and older.Expectant mothers must be accessing antenatal care services at either FF Ribeiro Clinic or Kgabo CHC.Expectant mothers and their partners must provide informed consent to participate in the study.

The inclusion criteria for health workers include:Health workers must be 18 years and older.Health workers must be knowledgeable about antenatal care and work with mothers and their partners.Health workers must provide informed consent to participate in the study.

There are no specific exclusion criteria beyond the inclusion criteria.

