#### Phase 2 sampling & data collection

During Phase 2 of the study, the randomized control trial, researchers and research assistants will randomly recruit women attending an antenatal care visit and their partners, inviting them to participate in the randomized control trial. Every participant will be required to provide informed consent before they can be included in the sample. Participants will be randomized into either the intervention group or the control group until the sample size of 420 has been reached. To implement the randomization, a table with the generated randomization sequence will be used, and as a participant agrees to participate in the study, they will be sequentially allocated to a row in the table that will determining the group that the participant will form part of. The sample size for the randomized control trial, was determined using the primary outcome of the study, change in knowledge. We will allocate participants equally to the treatment and control groups, through a balanced computer-generated random sequence. We use a 0.05 level of significance (*P* < 0.05) and a power of 0.9 with a two tailed test for significance.

Our hypothesis is that at the 3-month follow-up, participants in the control group will score 43% on the intention to change behavior score (12 points out of 28 points in the survey). We propose that after the 3-month follow-up the intervention group will score 61% (17 out of 28 points). This is an 18% absolute increase and a 1.41 times relative increase. A sample size of *n* = 140 was calculated for the intervention group and the control group. We then used an increase of 50% to account for potential participant drop-outs, bringing the sample size for the intervention group to *n* = 210 and the sample size for the control group to n = 210, spread equally and randomly across the two sites (Kgabo CHC[urban site] and Ga-Rankuwa[rural site]). Thus, a total of *n* = 420 participants for the entire randomized control trial will be required. These sample size calculations were carried out on G-Power 3.1.9.6.

Sample size calculations were based on the difference between two independent proportions using a z-test (Power: 0.9, Alpha 0.05, Allocation N1/N2: 1, p1 = 0.43, p2 = 0.61). The sample size per group was rounded up to the nearest 10 patients (N1 = 140, N2 = 140).

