Expectant mothers assigned to the intervention group will watch the 10 Amandla Mama videos and their partners will receive the same 10 Amandla Mama videos via the social media platform, WhatsApp or short messaging service (SMS). The expectant mothers will be asked to provide the researchers with their contact details and the contact details of their partners. Partners who agree to participate in the study and who provide informed consent will receive the Amandla Mama videos by SMS or WhatsApp. The control group will receive existing treatment as usual-antenatal care only.

After 3 months, knowledge, behavioral intent, and user satisfaction surveys will be administered telephonically to all participants. The follow-up is conducted after 3 months to test long-term retention providing a better predictor for ongoing change. The research assistants under supervision of the researchers, will administer the telephonic survey. Data collected from participants who discontinue with or deviate from the study will not be used.

Surveys for the expectant mothers consist of a total of 61 questions: 10 background questions, 15 behavioral intention questions, 30 knowledge questions and 8 user satisfaction questions (refer to Additional file 1: Annexure 2). Surveys for partners consist of a total of 63 questions: 8 background questions, 18 behavioral intention questions, 30 knowledge questions and 8 user satisfaction questions (refer to Additional file 1: Annexure 3). The user-satisfaction questions, which consider how satisfied the participants are with the Amandla Mama videos, will only be administered to participants in the intervention group. All Phase 2 study participants will receive ZAR 100 to compensate them their time and expenses incurred by participating in our study.

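### Partner entry is not tied to a time before the mother's allocation and is described only for the video arm, so the partner comparison is open to post-randomisation selection

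*Protocol article*

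**What the plan says.** All of the key text is in the protocol article, mostly under Phase 2 sampling & data collection.

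- **Invitation.** The opening paragraph says staff will "randomly recruit women attending an antenatal care visit and their partners, inviting them to participate in the randomized control trial".
- **Consent.** "Every participant will be required to provide informed consent before they can be included in the sample". The inclusion criteria under Study population agree: "Expectant mothers and their partners must provide informed consent to participate in the study".
- **Allocation.** It happens at the moment of agreement: "as a participant agrees to participate in the study, they will be sequentially allocated to a row in the table".
- **Partner's arm.** The later paragraph on video delivery makes the partner follow the mother: "Expectant mothers assigned to the intervention group will watch the 10 Amandla Mama videos and their partners will receive the same 10 Amandla Mama videos".
- **Route to the partner.** "The expectant mothers will be asked to provide the researchers with their contact details and the contact details of their partners".
- **Partner consent.** "Partners who agree to participate in the study and who provide informed consent will receive the Amandla Mama videos by SMS or WhatsApp".
- **Control arm.** That paragraph gives only usual antenatal care, with no step for partners.
- **Use of partner data.** The Methods overview below Fig. 1 says "Surveys will also be conducted with partners of the recruited expectant mothers in the study", without restriction by arm. Mock Table 3 has a row for partners' behavioural intentions with a relative risk, confidence interval and P-value by arm. It also has a single Knowledge Score row, not split into mothers and partners, although both surveys contain 30 knowledge questions.

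**The concern.** A randomised comparison of partners needs each partner's entry into the trial to be independent of the arm. That holds if the partner consents before the row is revealed, or if consent does not depend on the arm in a way related to the outcome. The text secures neither. It lets staff allocate the mother when she agrees and reach the partner afterwards by telephone. The only terms on which it describes partner consent are those of the video arm. Under Sampling and data collection, the same staff both enrol and assign participants, so the person approaching the partner can know the arm.

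If the kind of partner who consents differs by arm, the partner relative risk mixes the effect of the videos with the effect of who agreed to join. No later analysis can repair this, because partners who decline supply no survey data. Effects on partners as well as women are part of the study's stated aim. Knowledge is the primary outcome, and nothing in the article keeps partners' answers out of its single row.

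**Working it through.** **Step 1: set the two descriptions side by side.** The plan has no figure for partner consent to reproduce, so the check starts with the text.

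| Question | Opening paragraph | Paragraph on video delivery |
|---|---|---|
| Who is invited? | Women and partners | Mothers, then partners through details she gives |
| What decides the partner's arm? | A row taken when a participant agrees | The mother's assignment |
| Consent in the control arm? | Yes, by the general rule | No partner step described |
| Partner asked before the mother's row is known? | Not stated | Not stated |

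**Step 2: try the possible readings.**

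1. *Each person takes a row.* This follows the opening paragraph literally. A partner could then be in a different arm from the mother, which contradicts the later paragraph.
2. *The couple consents together and takes one row.* This fits the joint invitation. It does not explain why partner details are then collected from the mother, or why partner agreement appears only on the way to the videos.
3. *The mother takes a row and the partner is asked later.* This fits the later paragraph and does not break the general consent rule, because consent before inclusion in the sample is not the same as consent before the mother's row is known.

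The text does not choose between readings 2 and 3. Only reading 2 protects the partner comparison by design.

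**Step 3: illustrate what reading 3 could do.** The documents give no consent rates, so every consent rate and engagement share here is an assumption. Suppose half of partners are engaged (mean score s1) and half are not (s0), and the videos have no effect. With consent probabilities a (engaged) and b (not engaged), the mean score among consenting partners is

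M = (a·s1 + b·s0) / (a + b).

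Set A uses s1 = 61% and s0 = 43%. These are the plan's hypothesised arm scores, borrowed only as a plausible spread. Set B uses 55% and 35%.

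| Set | Video a / b | Control a / b | Overall consent, video vs control | Mean, video vs control | Difference (points) | RR |
|---|---|---|---|---|---|---|
| A | 80 / 60 | 80 / 20 | 70% vs 50% | 53.3 vs 57.4 | −4.1 | 0.93 |
| A | 80 / 50 | 80 / 30 | 65% vs 55% | 54.1 vs 56.1 | −2.0 | 0.96 |
| B | 60 / 60 | 60 / 60 | 60% vs 60% | 45.0 vs 45.0 | 0.0 | 1.00 |
| B | 70 / 50 | 60 / 60 | 60% vs 60% | 46.7 vs 45.0 | +1.7 | 1.04 |
| B | 80 / 40 | 60 / 60 | 60% vs 60% | 48.3 vs 45.0 | +3.3 | 1.07 |
| B | 80 / 20 | 60 / 60 | 50% vs 60% | 51.0 vs 45.0 | +6.0 | 1.13 |

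First row written out: video (0.8 × 61 + 0.6 × 43) / 1.4 = 53.3; control (0.8 × 61 + 0.2 × 43) / 1.0 = 57.4; ratio 53.3 / 57.4 = 0.93.

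Two things follow. Bias arises only if a/b differs between arms, and its sign depends on which partners the videos attract. Equal overall consent is also no proof of safety: with 60% in both arms, the ratio can still be 1.04 or 1.07.

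**The case against.** The strongest reply is that the opening paragraph already puts things in the right order: partners are invited with the women, everyone consents before inclusion, and allocation follows agreement. The inclusion criteria and the Ethical considerations section also require consent without distinction by arm. The sentence on partner consent may only say who is sent videos. The Phase 2 consent form is not shown, and an article may leave enrolment logistics to the full protocol.

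Much of this stands, and it rules out several stronger readings:

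- A reader might infer that partners are always approached after the mother's arm is known. No sentence says so; that inference rests on sentence order.
- A reader might infer that the partner groups are simply self-selected. That would require consent to differ by arm in an outcome-related way, which is possible but not shown.
- A reader might infer that control partners are offered nothing for joining. The section pays all Phase 2 participants ZAR 100, which softens any difference in incentive; the videos remain a difference.
- A reader might infer that a partner's refusal makes a randomised mother ineligible. Study population keeps mothers without partners eligible, and the delivery paragraph foresees partners who decline without any consequence for her. The natural reading is that each person consents individually.

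The reply does not remove the conflict. The opening paragraph, applied literally to partners, contradicts the rule that they follow the mother's arm. Once they follow it, the general consent rule no longer guarantees consent before her allocation. This goes beyond a detail left to a fuller document, because the article does set out the partner step, and does so for one arm only.

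**Conclusion.** The concern holds as an unreconciled description of partner entry that permits arm-dependent enrolment. The partner row of mock Table 3 is open to post-randomisation selection, and so is the Knowledge Score row if partners' answers enter it.

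The size is unknown and the sign can go either way. The range of 0.93 to 1.13 shows only what assumed consent patterns could produce without any video effect; it is not an estimate, and it shrinks to 1.00 when consent patterns match across arms.

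The mothers' comparison stays randomised and is unaffected on this point if analysed separately. This is therefore a correction worth making before recruitment continues, and one needed for any causal claim about partners, but not a flaw in the trial as a whole.

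**What to change.** Reconcile the two paragraphs under Phase 2 sampling & data collection as follows.

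1. State that the unit randomised is the mother, together with her partner if she has one.
2. Take partner contact details from every mother before her row is revealed.
3. Invite and consent partners in both arms with the same arm-neutral script, before the row is revealed wherever the partner can be reached.
4. Report partners identified, approached and consented by arm. Because equal totals do not exclude bias, do not treat matching counts as sufficient reassurance.
5. If some partners are consented after allocation, flag them and show the partner comparison restricted to those consented before it.
6. Say whether partners' answers enter the Knowledge Score row; if so, show mothers separately.

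The cost is new wording, a slightly longer enrolment step, and possibly a smaller partner set in the restricted comparison. Barring all later partner recruitment would be cleaner, but could lose many partners, since the plan relies on reaching them by telephone. Flagging and restricting keeps them. The registration data set in the abstract lists recruitment as suspended with 29 participants enrolled, so the change is inexpensive now; it cannot be applied retrospectively to partners already approached.

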#### Phase 2 data analysis

For Phase 2 of the study, descriptive statistics will be collected and reported to compare the two groups. Confounders that will be measured include demographic characteristics of age, education, race group, religion, nationality, employment and earnings. Another confounder that should be balanced is the exposure of participants to Mom-Connect, an online platform that provides mothers with information about maternal and neonatal care. Confounders will be reported by video intervention and treatment as usual (TAU) across rural and urban sites and overall, for the entire cohort (see mock Table 1). Since this is a large enough randomized control trial the confounders should be balanced. We will compare differences between the control and intervention groups in knowledge and intended behavior change at a 3-month follow-up.

**Table 1 Tab1:** Mock table of confounders

Socio-Demographic Variables		Urban			Semi-Rural			Overall		
Variable Groupings	Individual Variables/ Questions	Video Intervention	TAU ANC Brochure	*P*-value	Video Intervention	TAU ANC Brochure	P-value	Video Intervention	TAU ANC Brochure	*P*-Value
	Age									
	Standard/grade									
Race	Race 1									
	Race 2									
	Race 3									
Religion	Religion 1									
	Religion 2									
	Religion 3									
Nationality	Nationality 1									
	Nationality 2									
	Nationality 3									
	Employment									
	Earnings									
	Partnership status									

The outcome variables will also be described overall and by rural and urban sties (see mock Table 2). The reported effect size will be an unadjusted relative risk using Poisson regression. Rates for Poisson regression will be total correct answers divided by total questions. This keeps with the intention to treat paradigm, so questions not attempted or answered as “don’t know” are included as incorrect answers).

**Table 2 Tab2:** Mock table of outcome variables

Variable Groupings	Individual Variables/ Questions	Urban (%)	Semi-Rural (%)	***P***-Value
**Behavioural intentions Mothers**	Attend ANC appointments			
	Own HIV status known			
	Partner HIV status known			
	Take partner to ANC			
	Drink alcohol			
	Wash hands			
	Wear a mask			
	Breastfeed			
	Eat green vegetables			
	Eat fruit			
	Eat meat			
	Take partner to birth			
	Feel fetal kicks			
	Vaccinate child			
	Hold baby			
**Behavioural intentions Partners**	Go to ANC visit			
	Physically enter ANC			
	Pay ANC costs			
	Remind about ANC			

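### Discarding data from participants who discontinue or deviate is a post-randomisation exclusion that conflicts with the plan's intention-to-treat label

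*Protocol article*

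**What the plan says.** Three statements in the Protocol article bear on who is analysed.

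- **Exclusion (Phase 2 sampling & data collection):** "Data collected from participants who discontinue with or deviate from the study will not be used". No exception is given, and neither discontinuing nor deviating is defined.
- **Follow-up (same section):** "knowledge, behavioral intent, and user satisfaction surveys will be administered telephonically to all participants". Outcomes are therefore to be sought from everyone, adherent or not.
- **Analysis principle (Phase 2 data analysis):** "This keeps with the intention to treat paradigm, so questions not attempted" or answered with a don't-know count as incorrect.

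The arms differ in what they ask of participants. "Expectant mothers assigned to the intervention group will watch the 10 Amandla Mama videos", and partners receive the same videos by WhatsApp or SMS. For controls: "The control group will receive existing treatment as usual-antenatal care only".

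Nowhere does the article say that all randomised participants are analysed in their allocated arm, and it names no separate full analysis set.

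**The concern.** The exclusion is a positive instruction to discard data already collected, so it is not a detail left to an analysis plan. It selects participants on behaviour after allocation, whereas intention to treat keeps them in the comparison whatever they did. The one feature offered as intention to treat governs how an item is scored and says nothing about who is analysed.

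The selection can differ between arms. Failing to watch the allocated videos is an obvious form of deviation, and only the intervention arm can do it. If those who do not watch are also those who would score lower on knowledge, the primary outcome, removing them raises the video-arm mean with no help from the videos. A larger sample does not remove such a bias. Because a deviation is undefined, exclusions could also be settled after outcomes are known.

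**Working it through.** **The plan's own figures.** The planned difference is 0.61 − 0.43 = 0.18, or 18 points (Phase 2 sampling & data collection). The article states it for the intention score and gives no separate figure for knowledge, so it serves here only as a yardstick. The inflation step reproduces: 140 × 1.5 = 210 per group, 420 in total. The 140 itself does not follow from the stated two-tailed test (a pooled z-test gives 160 per group), but that is a separate matter and nothing below depends on it. The article gives no rate of deviation, no score SD and no link between engagement and score, so these are assumed.

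**Illustration 1: the least engaged are dropped from one arm, with no true effect.** Let engagement be standard normal with correlation r to the score, and drop the lowest fraction f. The retained mean shifts by r × φ(k)/(1 − f) SD, where k is the f-quantile.

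- f = 0.20: k = −0.842, φ(k) = 0.280, φ(k)/(1 − f) = 0.280/0.80 = 0.350
- r = 0.3: 0.3 × 0.350 = 0.105 SD
- r = 0.5: 0.5 × 0.350 = 0.175 SD
- In points: 0.105 × 15 = 1.6 at the low end and 0.175 × 20 = 3.5 at the high end

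**Illustration 2: a different model, to show the range.** Both arms have a true mean of 43%. A fraction f of the intervention arm is excluded, and their scores are g points below those retained. The spurious difference is f × g. The last column is the two-sided rejection rate at nominal 5% from the two-proportion test used for the sample size, with 210(1 − f) against 210 participants.

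| f | g (points) | f × g (points) | Rejection rate |
|---|---|---|---|
| 10% | 5 | 0.5 | 5.1% |
| 10% | 10 | 1.0 | 5.5% |
| 10% | 20 | 2.0 | 6.9% |
| 20% | 5 | 1.0 | 5.4% |
| 20% | 10 | 2.0 | 6.8% |
| 20% | 20 | 4.0 | 12.2% |

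For f = 20% and g = 10: 168 participants at 0.45 against 210 at 0.43. The null SE is √(0.4389 × 0.5611 × (1/168 + 1/210)) = 0.0514. The rejection rate is about Φ((0.02 − 1.96 × 0.0514)/0.0514) + Φ((−0.02 − 1.96 × 0.0514)/0.0514) = 0.058 + 0.009, that is 6.8% before rounding.

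That test treats each participant as a single yes or no. A comparison of mean scores is more precise, so the same 2-point bias matters more. With an assumed SD of 20 points the SE is 20 × √(1/168 + 1/210) = 2.07 points and the rejection rate is 16.2%. With an SD of 15 points it is 25.1%.

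**The case against.** **The two statements can operate together.** The intention-to-treat phrase is attached to item scoring, so retained surveys could be scored that way after the exclusions. This is fair: the article does not declare two incompatible analysis sets. It still applies the name to an analysis whose exclusion rule departs from it, so the conflict with the label stands.

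**The direction of bias is not established.** A deviation is undefined, and the article describes no record of who watched. Controls can also discontinue, and might see the videos because both arms attend the same two clinics. Exclusions among controls could add to the bias or offset it. This also stands, and it is why the direction is stated conditionally.

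**The size is modest.** Shifts of 1.6 to 3.5 points are well below 18 and rest on assumed inputs. That is true, but a small avoidable bias remains a bias, and it matters more if the real effect is smaller than planned.

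Two stronger readings are tempting, and the documents do not support them:

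- *Participants lost to follow-up would be scored as all incorrect, so unequal dropout would create a false effect.* The scoring rule speaks of questions, and the exclusion sentence would remove discontinuers before any scoring.
- *The sample size implies that about a third of participants would be discarded.* The calculation carries an "increase of 50% to account for potential participant drop-outs", and 140/210 does allow for losing one third. That allowance is for drop-outs, most of whom would have no 3-month survey to discard. The article gives no figure for participants who are surveyed and then excluded.

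**Conclusion.** The exclusion sentence is wrong as written and should be changed before analysis. It removes surveyed participants for post-randomisation behaviour, contradicts the intention-to-treat label, and is repaired nowhere else in the article. That conclusion needs no assumption.

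Direction and size do need assumptions. If deviation mainly means unwatched videos, and if less engaged participants score lower, the bias favours the videos. Under the first illustration it is 0.105 to 0.175 SD, or about 1.6 to 3.5 points. Under the second it is 0.5 to 4 points. Neither model approaches 18 points, so the rule alone would not produce an effect of the planned size.

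**What to change.** 1. Delete the exclusion sentence, or limit it to data whose use the participant has withdrawn.
2. State that every participant with a 3-month survey is analysed in the allocated arm, whether or not the videos were watched.
3. Keep any adherent-only analysis as a secondary analysis, with adherence defined in advance.
4. In Phase 2 data analysis, describe the counting of unattempted and don't-know items as incorrect as a scoring rule for completed surveys, not as intention to treat.

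Imputing missing surveys from enrolment data is not part of this fix. The background questions belong to the 3-month survey, and the article describes only contact details being collected at enrolment.

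The cost is wording, since the survey of all participants is already planned. The estimate becomes the effect of offering the videos, which non-viewing can dilute. If non-viewers gain nothing (assumed), 18 points becomes 18 × 0.9 = 16.2 at 10% non-viewing and 18 × 0.8 = 14.4 at 20%. Two-sided power is then 91.6% and 84.2% with 210 surveyed per group, or 77.7% and 67.5% with 140. The abstract's registration data set reports 29 enrolled and recruitment suspended, without naming the phase, so on that report the change could come before most outcome data are collected.

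### As written, background data come only from the 3-month telephone survey, so Table 1 would describe responders rather than the randomised groups, and the unadjusted RR gives up available precision

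*Protocol article*

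**What the plan says.** All references are to the Protocol article.

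- **Timing of the survey.** In Methods, in the text after Fig. 1: "These will be administered to patients 3 months after receiving the intervention". Under Phase 2 sampling & data collection: "After 3 months, knowledge, behavioral intent, and user satisfaction surveys will be administered telephonically to all participants". No other Phase 2 data collection is described.
- **Content of the survey.** For mothers: "Surveys for the expectant mothers consist of a total of 61 questions: 10 background questions, 15 behavioral intention questions", followed by the knowledge and satisfaction items. For partners: "Surveys for partners consist of a total of 63 questions: 8 background questions, 18 behavioral intention questions", followed by the same two blocks.
- **Incomplete participants.** The same section adds: "Data collected from participants who discontinue with or deviate from the study will not be used".
- **Confounders.** Phase 2 data analysis says: "Confounders that will be measured include demographic characteristics of age, education, race group, religion, nationality, employment and earnings". It continues: "Another confounder that should be balanced is the exposure of participants to Mom-Connect". No time of measurement and no time window for Mom-Connect are given. Mock Table 1 compares the arms on eight variables: age, grade, race, religion, nationality, employment, earnings and partnership status. Mom-Connect is not among them.
- **Balance and estimator.** The section expects balance because of the trial's size. Separately, it states: "The reported effect size will be an unadjusted relative risk using Poisson regression".

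**The concern.** A table of baseline characteristics has two jobs. It shows what the randomised groups looked like, and it lets a reader compare those who were lost with those who stayed. Both need data on everyone randomised, collected before allocation could influence the answers. If the background questions are asked only in the 3-month call, neither job can be done. The table would then compare responders with responders, and randomisation does not promise balance between those two groups.

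This matters here because participants evidently know their arm (videos or usual care only) and the outcome is collected by telephone. Loss related to arm is therefore plausible. Exposure to Mom-Connect is the one confounder that the plan singles out beyond demographics. Measured at 3 months with no time window, it could include use begun after the videos were watched. It would then be neither a clean check of balance nor a safe covariate. Finally, with no pre-allocation covariates, the analysis has little to adjust for beyond site, although education and prior exposure to health messages are likely predictors of a knowledge score.

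**Working it through.** **1. Is the background block part of the 3-month survey?** The inputs are the item counts under Phase 2 sampling & data collection.

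| Survey | Background | Intention | Knowledge | Satisfaction | Sum with background | Sum without | Stated total |
|---|---|---|---|---|---|---|---|
| Mothers | 10 | 15 | 30 | 8 | 63 | 53 | 61 |
| Partners | 8 | 18 | 30 | 8 | 64 | 56 | 63 |

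Neither sum matches its stated total exactly, which is a separate slip. With the background block the totals differ by 2 and 1. Without it they differ by 8 and 7. The stated totals therefore count the background questions as part of the survey. A block of 8 to 10 items also fits the eight variables in mock Table 1, which are listed in a column for individual variables or questions.

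**2. How many could be missing from Table 1?** The plan raises 140 per arm by 50%: 140 × 1.5 = 210, which reproduces its figure. The loss this covers is 1 − 140/210 = 33.3%, or 210 − 140 = 70 per arm. (The derivation of 140 is a separate matter and is taken as given.) For assumed loss rates, out of 210 per arm:

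| Loss | With background data | Without |
|---|---|---|
| 10% | 189 | 21 |
| 20% | 168 | 42 |
| 33.3% | 140 | 70 |

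**3. How far does size alone secure balance?** For a binary characteristic with 50% prevalence (assumed), the 95% range of the chance difference between arms is ±1.96 × √(0.25 × 2/n).

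- n = 210 per arm, all randomised: ±9.6 percentage points.
- n = 140 per arm, responders at the full allowance: ±11.7 points.
- n = 70 per arm within one site (140/2, as recruitment is split equally over two sites): ±16.6 points.

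These ranges cover chance only. Any selective loss comes on top and does not shrink with sample size.

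**4. Which items are exposed to change after randomisation?**

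- Not plausibly changed by the videos: age, race and nationality, and largely education and religion. Asked late, they suffer only from missingness.
- Able to change within 3 months: employment, earnings, partnership status, and Mom-Connect exposure if it is asked then.

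**5. What might adjustment be worth?** In a linear model, adjusting for covariates that explain a share R² of the outcome variance is equivalent to multiplying the sample by 1/(1 − R²). The documents give no R², so a range is assumed and applied to 140 responders per arm.

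| R² (assumed) | 1/(1 − R²) | Equivalent of 140 per arm |
|---|---|---|
| 0.05 | 1.05 | 147 |
| 0.10 | 1.11 | 156 |
| 0.20 | 1.25 | 175 |

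For a Poisson relative risk this is an approximation. Part of the gain would come from site, which is already known for everyone.

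**The case against.** The strongest reply is that the timing is inferred. No sentence says when the confounders are measured. The list of what is administered by telephone names knowledge, intent and satisfaction but not background. The item lists are in annexures that are not shown, and a condensed article may leave enrolment forms to the full protocol. This stands as a limit on certainty. It does not remove the point, because the article does say what the survey contains and when the survey is given. In addition, the rule that discards data from those who discontinue or deviate could keep lost participants out of Table 1 even if an enrolment form exists.

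Other objections stand in full and mark readings that the documents do not support:

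- A reader might infer that nothing would be known about those lost, or that differential loss could not be detected. That goes too far. Each participant takes a row in the randomisation table and is recruited at a known clinic, so arm and site are known and loss by arm is a simple count. Only the demographic make-up of those lost would be missing.
- A reader might infer that all the confounders become post-randomisation variables. Most cannot be altered by watching videos.
- A reader might take Mom-Connect to be one of the survey's background items. The article does not show this, and mock Table 1 omits it. That the videos would change its use is possible but not documented.
- A reader might infer that the unadjusted RR is an error, or that the plan justifies it by the trial's size. It is a valid estimate in a randomised trial, and the plan links size only to expected balance.
- The dropout allowance is a margin for potential losses, not a forecast.

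**Conclusion.** The point holds in limited form. On the article's own description, Table 1 would characterise telephone responders rather than the randomised groups. The demographic profile of up to 70 of 210 per arm (33.3%, the most that the plan's allowance covers) would be unknown. Employment, earnings, partnership status and possibly Mom-Connect exposure would be recorded after randomisation. This rests on reading the 3-month survey as the only source of background data, which is a strong inference rather than an explicit statement.

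The unadjusted RR is a missed opportunity for precision and does not make the analysis invalid. The potential gain of about 5 to 25% depends on an assumed R² of 0.05 to 0.20 and a linear-model approximation. The fix is worth making because it is cheap and because enrolment values of changeable items cannot be recovered later.

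**What to change.** 1. Ask the existing background questions, plus Mom-Connect use to date, after consent and before the group is revealed. State this timing in the protocol. If it is already done, one sentence saying so is enough.
2. Report Table 1 for all randomised participants by arm, add Mom-Connect to it, and give a second version by responder status within arm.
3. Exempt these enrolment data from the rule that discards data of participants who discontinue or deviate.
4. Prespecify an RR adjusted for site and a few enrolment covariates, for example age, education and enrolment Mom-Connect use, with the unadjusted RR reported alongside.
5. Do not adjust for any item measured at 3 months that the videos could change.

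The cost is a few extra minutes at enrolment, offset by a shorter telephone call. The only question that may be new is Mom-Connect use. The trial registration data set in the article lists 29 of a planned 450 participants enrolled and recruitment suspended, without saying in which phase, so most Phase 2 participants could still be covered. For anyone already randomised, fixed items can still be asked later, and should be marked as collected after allocation.
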